In designing this trial, our approach is guided by two principles. We wanted the intervention to reflect the improvements made in the field recently, including high-dose rifampicin and addition of fluoroquinolones and aspirin. We propose a novel clinical trial to demonstrate the efficacy of short course therapy compared to standard of care. The drugs and doses proposed in this trial have individually been shown to be beneficial and efficacious in the treatment of pulmonary tuberculosis and TB meningitis. However, they have not been evaluated for cumulative benefit. The INTENSE TBM trial that used high-dose rifampicin and linezolid evaluated mortality alone as an outcome and considered 30% reduction in mortality [14]. We hypothesize that intensified short course (6 months) ATT with high-dose rifampicin and moxifloxacin given along with corticosteroids and aspirin will significantly reduce mortality and disability in adults with TBM compared to 12 months of standard ATT regimen. We assume our study regimen will be superior to the control regimen in terms of reducing death or disability by at least 20%.

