### Sample size

The trial is powered to assess the superiority of intensified regimen (arm 1) compared to control regimen (arm 3). A systematic review and meta-analysis on treatment outcomes in TBM done by Stadelman et al. reported the proportion of mortality and disability after treatment is 24% and 32%, respectively [7]. The proportion of composite outcome (death or disability) is 56%. We assume a 20% reduction of composite outcome with our intervention (i.e., from 56 to 36%). We used the formula for Z test for comparing proportion between two groups (arm 1 and arm 3). Hence, to study the impact of “Intervention” compared to “Standard care” in reducing the composite outcome (death or disability), expecting a minimum difference of 20% between intervention arm with aspirin (arm 1) and control arm (arm 3), assuming 85% power of the study, 5% level of significance, 2-sided significance test; the required sample size was 112 patients in each arm. Considering 10% lost to follow-up, the total sample size was calculated as 372 with 124 in each arm. Previous clinical trials in TBM have evaluated mortality as an outcome and considered 30% reduction [14]. Since we propose to evaluate composite outcome of death or disability, we have assumed a conservative effect size of 20% reduction. The 10% loss to follow-up is assumed based on the previous TBM trials as well as randomized controlled trials conducted at ICMR-NIRT, Chennai [20, 21].

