The analysis for the primary outcome will be stratified based on HIV status and baseline severity of the disease measured by MRC. Sensitivity analysis will also be done including only definite and probable cases of TBM. The Cox proportional regression will be summarized using hazard ratio and 95% confidence interval. Extended Cox regression will be used in lieu of proportion Cox regression if the proportional hazard assumption is violated. The AE data will be summarized using frequency and percentage and compared between the regimens using Chi-square test. In addition, count regression models will be used to compare the number of AEs between the regimens after adjusting for other variables. Maximum plasma concentration (*C*max), time for maximal concentration (*T*max), and area under the curve (AUC) will be measured and correlated with treatment outcomes and occurrence of adverse events using log binomial regression model. Influence of PK parameters on treatment outcome will be identified using multivariable regression analysis. The quality of life will be summarized using mean and standard deviation. The variable will be compared between the regimens using ANOVA or the non-parametric alternative, Kruskal–Wallis test.

We will deal the missing data using multiple imputation technique depending on the missing data mechanism.

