### Outcome measures

Our primary outcome is mortality or disability which will be measured between inclusion and month 12 and month 24, i.e., time from randomization to death or disability during the follow-up period. All-cause mortality also will be considered as an outcome in the study. Survivors will be censored at the date they were last known to be alive (i.e., date of last follow-up visit, loss to follow-up or withdrawal). All-cause mortality rate will be measured in proportion and disability will be measured by modified Rankin scale. We will classify the score as “no disability” (a score of 0), “mild to moderate disability” (score of 1–2), and “severe disability” (3–5).

Grade 3 or 4 AEs will be measured in proportion according to Division of AIDS (DAIDS) criteria at the end of 12 months [18]. The DAIDS criterion categorizes adverse events as “mild events” (grade 1), “moderate events” (grade 2), “severe events” (grade 3), and “potentially life threatening events” (grade 4). Pharmacokinetic outcome measures will be plasma concentration time-curve during the dosing interval (AUC), peak plasma concentration (*C*_max_), and CSF concentration. Time to reach maximum plasma concentration (*T*_max_) of the study drugs will be measured up to week 8. Quality of life at baseline and 6 months, 12 months, and 24 months will be assessed in mean and standard deviation using a WHO Short form-36 (SF-36) questionnaire. It is a commonly used generic health-related quality of life (QoL) instrument which consists of 36 questions measuring health in different dimensions covering physical, mental, and social well-being of the patients. SF-36 was adapted and translated into several language and its validity and reliability were already established in India in TB context [22, 23].

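### SF-36 is to be compared by an unadjusted ANOVA or Kruskal–Wallis test although it is measured at enrolment, which gives away precision; handling of deaths also needs a rule

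*Protocol article*

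**What the plan says.** The Objectives section makes the comparison of health-related quality of life between intervention and control arms a secondary objective. Outcome measures gives the timing and summary: "Quality of life at baseline and 6 months, 12 months, and 24 months will be assessed in mean and standard deviation". The study schedule (Table 1) ticks the quality of life assessment at enrolment, so a baseline score is planned for every participant who can give one.

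Data analysis then fixes the method. The summary is "The quality of life will be summarized using mean and standard deviation" and the test is "The variable will be compared between the regimens using ANOVA or the non-parametric alternative", the alternative being the Kruskal–Wallis test. No baseline covariate, change score or repeated-measures model is named for SF-36. The same section does state adjustment for other outcomes: the primary analysis is stratified by HIV status and baseline MRC severity, and the adverse-event count models adjust for other variables.

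On missing data there is one sentence for the whole trial: "We will deal the missing data using multiple imputation technique depending on the missing data mechanism". It does not mention death. The Background hypothesis is that the intensified regimen "will significantly reduce mortality and disability in adults with TBM compared to 12 months of standard ATT regimen", and the Sample size section takes from a meta-analysis that "the proportion of mortality and disability after treatment is 24% and 32%, respectively".

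**The concern.** Two things stand out.

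The main one is that the plan pays for a baseline SF-36 and then names a test that ignores it. Part of the spread in follow-up scores is likely to be predictable from the score at enrolment. An unadjusted ANOVA leaves that part in the error term, so intervals are wider and power is lower than the same data could give.

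The secondary one is that a participant who has died has no SF-36 score. If the trial's own mortality hypothesis is right, the arms will differ in who can be scored, and the observed means may then compare differently selected survivors. The imputation sentence does not settle this. Applied to deaths, it would create quality-of-life scores for people who are no longer alive. Not applied to them, it leaves a comparison among survivors.

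**Working it through.** **The plan's own figure.** The article gives no SF-36 standard deviation, target difference or power. The only sample-size figure is for the composite outcome (56% versus 36%, two-sided 5%, 85% power): 112 per arm. The pooled-variance formula gives 110, and power at 112 is 85.6%. So that figure reproduces, but it does not bear on SF-36. It serves below only for the number of patients.

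**Step 1: precision lost by omitting baseline.** Input: the correlation r between enrolment and follow-up SF-36, which is assumed. Formula: residual variance with adjustment ÷ residual variance without = 1 − r². The equivalent gain in sample size is 1/(1 − r²).

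| r (assumed) | 1 − r² | equivalent sample size |
|---|---|---|
| 0.2 | 0.96 | 1.04 × |
| 0.3 | 0.91 | 1.10 × |
| 0.5 | 0.75 | 1.33 × |
| 0.7 | 0.51 | 1.96 × |

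**Step 2: the same in detectable difference.** Take 112 followed per arm and, for illustration, 24% deaths in both arms: 112 × 0.76 = 85.1 scored per arm. The pairwise difference detectable at 80% power, in SD units, is (1.96 + 0.84) × √(2/85.1) = 0.43. With adjustment it is multiplied by √(1 − r²): 0.41 at r = 0.3, 0.37 at r = 0.5 and 0.31 at r = 0.7.

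**Step 3: size of the death problem, by illustration.** Control mortality is 24%, the article's reference figure. Arm 1 mortality is not given, because the assumed 20-point benefit is on the composite and is not split into death and disability. Assume 15%, close to the proportional figure 24% × 36/56 = 15.4%. Assume also that everyone who would survive on control would survive in arm 1. Then:

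- Extra survivors as a share of arm 1 survivors = (0.24 − 0.15)/(1 − 0.15) = 10.6%. With 15.4% mortality the share is 10.1%.
- With 124 per arm and 15.4% mortality in arm 1: about 30 control deaths and 19 arm 1 deaths, leaving 94 and 105 survivors.
- If the extra survivors score 10, 20 or 30 points below the rest (assumed), the arm 1 mean falls by 0.106 × 10, 20 or 30 = 1.1, 2.1 or 3.2 points with nobody's quality of life made worse.

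**Step 4: effect on the test.** A simulation used 124 per arm, 10% loss, 24% control mortality and no true SF-36 effect. The frailest patients die, and frailty correlates 0.3 to 0.7 with quality of life. A nominal 5% two-arm test on survivors rejected in about 6% to 10% of trials at 15.4% arm 1 mortality, and in about 5% when mortality was equal. At the extreme where all 20 points of benefit are deaths averted (24% − 20 points = 4% mortality), it rejected in 9.5% to 36.7%.

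**The case against.** The best case for the plan as it stands is this. SF-36 is secondary, the trial is sized on the composite, and covariates for a secondary score are routine content for a statistical analysis plan that is not shown. Leaving baseline out of a randomised comparison does not bias it. The correlation may be low, because enrolment falls in acute meningitis, and at r = 0.3 the detectable difference improves only from 0.43 to 0.41 SD. The sickest participants, some consented through a representative because of altered sensorium, may have no baseline score at all.

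Most of this limits the size of the point but does not remove it. The article does not leave the method open. It names an unadjusted test for SF-36 in the section where it states stratification or adjustment for other outcomes, so a later analysis plan using ANCOVA would depart from it.

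Two stronger readings are tempting, and the document does not support them. A reader might infer that the plan restricts SF-36 to survivors. No sentence says so, and the general imputation sentence has to be read alongside the test. A reader might also infer that the comparison would hide or reverse a real benefit. A shift of roughly 1 to 3 points, resting on assumed mortality and assumed score gaps and with no SF-36 standard deviation to judge it against, does not show that. The larger distortion in the simulation needs all of the composite benefit to be deaths averted, which the article does not claim.

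It is also fair to say that baseline adjustment does not cure selection by death. Ranking deaths lowest mixes mortality, already part of the primary composite, into a quality-of-life result, so it belongs only in a sensitivity analysis.

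**Conclusion.** The point holds as one of precision, with a smaller point on deaths attached. The named SF-36 test leaves available baseline information unused. The cost is about 9% of residual variance at r = 0.3 and 25% at r = 0.5; both correlations are assumptions, and at r = 0.2 the cost is only 4%. There is no bias from this source, and no stated figure in the article changes.

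On deaths, what the document supports is that it hypothesises lower mortality on the intensified regimen and gives no rule separating death from missing SF-36. The observed means may therefore compare differently selected survivors. The illustration of about 10% extra arm 1 survivors rests on 24% versus an assumed 15% mortality, and on no one being harmed by arm 1 who would have survived on control. It shows the direction and a plausible order of size; it is not a prediction.

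**What to change.** 1. Replace the ANOVA with a baseline-adjusted comparison: ANCOVA, or a mixed model across visits, with enrolment SF-36 and MRC grade as covariates.
2. For participants too ill to complete SF-36 at enrolment, use a missing-baseline indicator or mean imputation of the baseline score, computed without regard to arm, so that they stay in the analysis.
3. State that SF-36 is not imputed after death and that multiple imputation applies only to scores missing in people who are alive. If a mixed model is chosen, say how visits after death are treated, since such a model otherwise handles them as ordinary missing values.
4. Show the number of deaths in each arm beside each SF-36 mean.
5. Add one sensitivity analysis: the Kruskal–Wallis test already named, with deaths given the lowest rank, labelled as a combined survival and quality-of-life comparison.

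The cost is a little analysis work, and no new visits, data or patients are needed. The small downside is the extra rule for missing baseline scores, which will apply mostly to the sickest participants and reduces the precision gained. The article's Trial status section says recruitment had not begun at this version, so the change could be fixed before any outcome data exist.

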### Trial monitoring

A Data Safety and Monitoring board (DSMB) will review data and monitor progress of the trial and to detect evidence of early safety issues for the participants. The DSMB will consist of TB clinicians, a pharmacokinetic specialist, and an independent biostatistician. The trial will be monitored by an independent trial monitor to verify the accuracy, completeness of the trial data and the conduct of the trial is in compliance with the applicable regulatory requirements and Good Clinical Practice (GCP). The IEC of ICMR- NIRT and all the participating institutes will also oversee the conduct of the trial.

### Outcome measures

Our primary outcome is mortality or disability which will be measured between inclusion and month 12 and month 24, i.e., time from randomization to death or disability during the follow-up period. All-cause mortality also will be considered as an outcome in the study. Survivors will be censored at the date they were last known to be alive (i.e., date of last follow-up visit, loss to follow-up or withdrawal). All-cause mortality rate will be measured in proportion and disability will be measured by modified Rankin scale. We will classify the score as “no disability” (a score of 0), “mild to moderate disability” (score of 1–2), and “severe disability” (3–5).

Grade 3 or 4 AEs will be measured in proportion according to Division of AIDS (DAIDS) criteria at the end of 12 months [18]. The DAIDS criterion categorizes adverse events as “mild events” (grade 1), “moderate events” (grade 2), “severe events” (grade 3), and “potentially life threatening events” (grade 4). Pharmacokinetic outcome measures will be plasma concentration time-curve during the dosing interval (AUC), peak plasma concentration (*C*_max_), and CSF concentration. Time to reach maximum plasma concentration (*T*_max_) of the study drugs will be measured up to week 8. Quality of life at baseline and 6 months, 12 months, and 24 months will be assessed in mean and standard deviation using a WHO Short form-36 (SF-36) questionnaire. It is a commonly used generic health-related quality of life (QoL) instrument which consists of 36 questions measuring health in different dimensions covering physical, mental, and social well-being of the patients. SF-36 was adapted and translated into several language and its validity and reliability were already established in India in TB context [22, 23].

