## Background

Tuberculosis (TB) is a devastating disease that leads to significant morbidity and mortality. According to the Global TB report of World Health Organization (WHO), 7.5 million individuals were newly diagnosed with TB and 1.3 million succumbed to the disease [1]. Tuberculous meningitis (TBM) is a severe form of TB with high mortality and morbidity. Even though TBM contributes to 2% of all TB cases in low HIV prevalence settings, it accounts for 20 to 69% short-term mortality with standard anti-tuberculosis therapy (ATT) [2–5]. The case fatality ratio for central nervous system (CNS) TB is about 35% among all forms of TB in India [6]. A similar proportion of patients are also severely disabled with TBM [7]. A nationwide population-based cohort study with a 30-year follow-up revealed that TBM patients in Denmark had nearly twofold increased long-term risk of mortality compared to the general population [8]. The most common complications associated with TBM include hydrocephalus, hemorrhage, arachnoiditis, and formation of tuberculoma. The most commonly reported long-term neurological sequelae are motor deficits, epilepsy, cognitive impairment, and cranial nerve palsies [9, 10]. Stroke occurs in 15–57% of patients, of whom 20% suffer long-term neurological deficits [11].

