### Data analysis

Participants who have completed 80% of the prescribed treatment will be considered for per protocol (PP) analysis and all the patients who were randomized will be taken for intention-to-treat analysis. Modified intent-to-treat (mITT) will be performed after excluding: (a) patients with DR TBM detected after randomization; (b) diagnosed to have any other meningitis such as bacterial, viral, and fungal after randomization; (c) patients refused to be part of the trial when the initial consent was obtained from legally authorized representative; and (d) receiving less than 2 months of administration of the randomized study drugs for reasons other than death.

An interim analysis is planned at two time points during the study period, viz. after 33% and 66% of the enrolled patients have completed 8-week treatment. In addition, the interim analysis may be done if the frequency of reported serious adverse events is greater than anticipated. Reports will be provided to the DSMB at these time points.

Baseline variables will be summarized between the groups using appropriate summary statistics based on the level of measurement. The time to composite outcome will be estimated using Kaplan–Meier survival estimate and it will be compared between the three arms using Log rank test. The factors associated with time to death or disability will be assessed using Cox proportional hazards regression analysis. This is a superiority trial and we will perform two-sided tests and use type I error alpha value of 5% to claim superiority between two groups.

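### The primary outcome is time to first death or disability, but disability can be present at entry and can recover, so it does not match the end-state proportion used to size the trial

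*Protocol article*

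**What the plan says.** - **Outcome measures** gives the primary outcome as "mortality or disability which will be measured between inclusion and month 12 and month 24", and then restates it as "time from randomization to death or disability during the follow-up period".
- **Outcome measures** also grades the Rankin score: 0 is no disability, 1–2 mild to moderate, 3–5 severe. It does not say which grade is the event.
- **Data analysis** says "The time to composite outcome will be estimated using Kaplan–Meier survival estimate" and "it will be compared between the three arms using Log rank test". Cox regression follows, and the primary analysis is to be stratified by HIV status and baseline MRC severity.
- **Table 1** schedules the Rankin score at screening, enrolment, weeks 1, 4 and 8, months 4, 6, 9 and 12, and then three-monthly to month 24.
- **Treatment allocation** foresees participants in MRC grades 1 to 3. **Ethical considerations** foresees consent by a representative where sensorium is altered or illness is severe, and re-consent once the participant is able to give it.
- **Sample size** adds 24% mortality and 32% disability after treatment to get 56%, and plans for 36% in arm 1. On method it says "We used the formula for Z test for comparing proportion between two groups (arm 1 and arm 3").

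**The concern.** Kaplan-Meier, log-rank and Cox on a composite use the first qualifying event, and later recovery cannot undo it. That suits death. Disability by Rankin score is a state: it may exist before the first dose, and it may improve. The re-consent provision shows that the protocol itself expects some impaired patients to recover.

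A clock that starts at randomisation, with a Rankin reading at enrolment and another at week 1, turns every patient disabled at entry into an event at about time zero. Treatment cannot have influenced these events, so they occur at the same rate in every arm. They dilute the contrast between arm 1 and arm 3, and they count patients who recover as failures. The Abstract's aim is disability-free survival, and the sample size takes disability after treatment as its input. The stated outcome measures neither for these patients.

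**Working it through.** **1. Reproduce the planned sample size.** Inputs from Sample size: p₃ = 0.56, p₁ = 0.36, two-sided 5%, 85% power. With pooled null variance and p̄ = 0.46:

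n = [1.96·√(2p̄(1−p̄)) + 1.036·√(p₃(1−p₃) + p₁(1−p₁))]² / (p₃ − p₁)²
= [1.96·0.7048 + 1.036·0.6905]² / 0.04 ≈ 110 per arm.

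The stated 112 is within two patients of this. Power at 112 per arm is Φ[(0.20·√112 − 1.96·0.7048)/0.6905] = Φ(1.065) = 85.6%. The sample size is therefore sound for a comparison of two end-state proportions.

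**2. Apply the outcome as written.** Two assumptions are needed, and neither comes from the documents:
- a share b of each arm is disabled at week 1 whatever the treatment;
- 56% v 36% holds among the rest.

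The ever-event proportions become b + (1−b)·0.56 and b + (1−b)·0.36, so the difference shrinks to (1−b)·0.20. Using the power formula of step 1 with 112 per arm:

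| b | arm 3 | arm 1 | difference | power | n per arm for 85% |
|---|---|---|---|---|---|
| 0 | 56.0% | 36.0% | 20 points | 86% | 110 |
| 10% | 60.4% | 42.4% | 18 points | 77% | 137 |
| 30% | 69.2% | 55.2% | 14 points | 58% | 214 |
| 50% | 78.0% | 68.0% | 10 points | 39% | 353 |

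**3. Repeat with the planned test.** An unstratified log-rank test was simulated under the same assumptions (112 per arm, Rankin read at the Table 1 visits to month 12, 1,500 replicates). Power was 87% at b = 0, 52% at b = 30% and 31% at b = 50%.

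**4. Allow for the MRC stratification.** In a stratified log-rank simulation, the stratum was assumed to match entry disability in 80%, 90% or 100% of patients. Power was 54%, 61% and 72% at b = 30%, and 37%, 42% and 59% at b = 50%. Stratification helps, but the patients who became events at week 1 still contribute nothing about their later course.

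**5. Check the alternative.** A fixed-visit composite at 56% v 36% needs 110 per arm, 110/0.9 = 122.2, so 123 with 10% loss, and 3 × 123 = 369 in total. The planned 372 covers it.

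**The case against.** **Baseline disability is not quantified.** This stands. Enrolling MRC grades 1–3 and allowing representative consent shows that some patients are impaired at entry, not that most are. The exclusion criteria also remove rapidly deteriorating and moribund patients. A reader might infer that disability is usual at entry and that the log-rank test merely scores the state at admission. The documents do not support that: deaths and new disability still contribute, so the contrast is diluted and not erased.

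**The power figures rest on a model.** This also stands. The 56% is an overall rate in the protocol, and applying it only to patients not disabled at entry is a simplification. Stratification by MRC grade reduces the loss.

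**Censoring.** A reader might take "Survivors will be censored at the date they were last known to be alive" to mean that disabled survivors are censored, so that the composite collapses to mortality. But the sentence directly follows the one naming all-cause mortality as an outcome, and reads naturally as the rule for mortality. It only needs to say so.

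**Sizing by Z test and analysing by log-rank.** This is not an error in itself. With no baseline disability, simulated log-rank power at 112 per arm is 87%, above the planned 85%.

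**The analysis plan may settle it.** A Rankin cut-off or a sustained-disability rule can be left to the full protocol or the analysis plan, and its absence from an article is no fault. The start of the clock and the time-to-event form, however, are stated here. Naming months 12 and 24 does not remove them, because the same sentence defines the outcome as a time from randomisation.

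**Conclusion.** The point holds as a mismatch between three stated elements: a time-to-first-event outcome that starts at randomisation, a disability measure that can be positive at entry and can reverse, and a sample size built on death or disability after treatment. The direction is clear: events already present at entry pull the arms together. The size is unknown because it depends on b. Under the simple model, two-proportion power is 86% at b = 0, about 77% at b = 10%, 58% at b = 30% and 39% at b = 50%, and part of the loss is recovered by MRC stratification. These figures illustrate the sensitivity of the design and do not estimate its actual power.

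One further reading should not be pressed. Background says "A similar proportion of patients are also severely disabled with TBM" and cites the same source from which Sample size takes its 32%, which it calls simply disability. A reader might conclude that the planning input means Rankin 3–5. That source is not at hand, and no passage equates the two. The cut-off has to be matched to the source by the sponsor.

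**What to change.** 1. Define the primary endpoint as death by, or disability at, one fixed visit counted from randomisation and common to all arms. Month 12 is in Table 1 for every arm.
2. Set one Rankin cut-off in advance, chosen by the sponsor to match the definition behind the 32% planning input. If the 56% v 36% does not apply at that cut-off and visit, revisit the sample size.
3. Compare arm 1 with arm 3 as a risk difference with 95% confidence interval, stratified by MRC grade and HIV status as planned. Use the planned multiple imputation for missing scores.
4. Keep Kaplan-Meier, log-rank and Cox for all-cause mortality, and state that the last-known-alive censoring rule applies to mortality only.

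**Cost.** This changes the primary outcome of a registered trial, so it needs a protocol and registry amendment, best made before recruitment; Trial status says recruitment had not begun. Information on when disability occurs is given up in the primary analysis. No extra visits are needed, and no extra patients if 56% v 36% holds for the chosen definition.

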### Participant timelines and follow-up

In this assessment, demographic details, medical history, clinical examination, neurological assessment including Modified Rankin Score (MRS) and Glasgow Coma Scale (GCS), sociological assessment for compliance to trial procedures, and all other study procedures will be done. Blood will be collected for hematological (complete blood count—CBC) and biochemical tests (sugar, HbA1C, liver, and renal function tests), HBsAg, and HIV. Patients will also undergo CT or MRI imaging of the brain. We will also collect sputum for CBNAAT and AFB culture and do chest X-ray to rule out pulmonary TB. All eligible patients will be enrolled into the trial. At the time of enrolment, blood will be collected for immunological biomarkers (CRP, TNF-α, monocyte and dendritic cell functions, and other cytokines).

During the study period, patients will be followed as per the study schedule attached (Table 1). After admission to the study and treatment allocation, participants will be followed up every week for the first 2 months and monthly till the completion of the treatment. They will undergo clinical examination including detailed neurological examination and adverse event (AE) monitoring. After treatment completion, all participants will be followed up once in 3 months for a period of 12 months. Participants in the study arms I and II will complete 12 months of post-treatment follow-up at the 18th month study visit and participants in the control arm will complete their post-treatment follow-up at the 24th month study visit.

**Table 1 Tab1:** Study schedule

S No	Investigations	Pre-screening	Screening	Enrolment	W1	W2	W3	W4	W5	W6	W7	W8	M3	M4	M5	M6	M7	M8	M9	M10	M11	M12	M15	M^a^18	M21	M24
1	Screening consent		✓																							
2	Assess eligibility		✓	✓																						
3	Informed consent			✓																						
4	History and clinical examination		✓	✓	✓	✓	✓	✓	✓	✓	✓	✓	✓	✓	✓	✓	✓	✓	✓	✓	✓	✓	✓	✓	✓	✓
5	GCS		✓	✓	✓	✓	✓	✓	✓	✓	✓	✓	✓	✓	✓	✓			✓			✓	✓	✓	✓	✓
6	Modified Rankin’s score		✓	✓	✓			✓				✓		✓		✓			✓			✓	✓	✓	✓	✓
7	Sputum smear and MGIT^b^		✓																			✓		✓		
8	CSF analysis for AFB smear, MGIT, Xpert, and to rule out other etiology as appropriate	✓																								
19	CSF cytology, biochemistry,	✓																								
10	HIV		✓																							
11	Urine pregnancy test^c^		✓					✓				✓	✓	✓	✓	✓	✓	✓	✓	✓	✓	✓				
12	Hepatitis B and C		✓																							
13	LFT		✓			✓		✓		✓		✓		✓		✓			✓			✓				

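### The only censoring rule, date last known alive, suits mortality rather than the death-or-disability primary endpoint; the expected effect is small and one sentence repairs it

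*Protocol article*

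**What the plan says.** Outcome measures in the protocol article defines the primary outcome as "time from randomization to death or disability during the follow-up period". Shortly after comes the only censoring rule in the document: "Survivors will be censored at the date they were last known to be alive". A parenthesis spells that date out as the last visit, the loss to follow-up or the withdrawal. The sentence between them reads "All-cause mortality also will be considered as an outcome in the study". The same section states that "disability will be measured by modified Rankin scale", and that mortality will be reported as a proportion.

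Data analysis plans Kaplan–Meier estimation, a log-rank test and Cox regression for time to the composite. It gives no other censoring rule, and mentions multiple imputation in general terms.

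Participant timelines and follow-up has participants "followed up every week for the first 2 months and monthly till the completion of the treatment". Treatment ends at month 6 in arms 1 and 2 and at month 12 in control. The section then says "After treatment completion, all participants will be followed up once in 3 months for a period of 12 months". In Table 1 the row "Modified Rankin’s score" is ticked after enrolment at W1, W4, W8, M4, M6, M9, M12, M15, M18, M21 and M24, whereas history and clinical examination are ticked at every visit. Patient compliance provides for telephone or home contact with absentees.

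**The concern.** A censoring date for a time-to-event endpoint should be the last time at which the participant was known to be free of the event. For death, that is the date last known alive. For death or disability, it is the last Rankin assessment that did not show disability.

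Under the stated rule, a participant whose last visit carried no Rankin score, or who was reached only by telephone, stays in the risk set after the last point at which disability was formally assessed. That time enters the denominator with no Rankin-based event able to occur in it, so the composite event rate is biased downward. The parenthesis adds to this, since a date of loss to follow-up or withdrawal may fall after the last visit. The visit schedule also differs between arms for part of the follow-up, so the unassessed time need not be equal.

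**Working it through.** **Planning figures, for context.** Sample size gives 56% v 36%, 85% power, two-sided 5%, 112 per arm. The pooled two-proportion formula gives n = [1.96·√(2·0.46·0.54) + 1.036·√(0.56·0.44 + 0.36·0.64)]² / 0.20² ≈ 110, close to the stated 112. Then 112/0.9 = 124.4, stated as 124, and 3 × 124 = 372. The point does not depend on these figures; they supply the event rates and the loss rate. Expected loss is 0.10 × 124 ≈ 12 per arm.

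**Step 1: visits set against Rankin assessments.**

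| | Control | Arms 1 and 2 |
|---|---|---|
| Visits without Rankin to M6 | W2, W3, W5, W6, W7, M3, M5 | the same seven |
| Visits without Rankin, M7–M12 | M7, M8, M10, M11 | none (visits at M9 and M12 only) |
| Total without Rankin | 11 | 7 |
| Largest gap, last Rankin to last visit, M7–M12 | M8 − M6 = 2 months; M11 − M9 = 2 months | 0 |
| Visits after M12 | all with Rankin | all with Rankin |

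The arms differ at scheduled visits only in months 7 to 12. The longer control follow-up (M24 against M18) adds no visit without a Rankin score.

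**Step 2: unassessed time and effect on the estimates.** A simulation compared control with one intervention arm, 124 each, 600 runs per scenario. Its assumptions are not from the protocol: exponential hazards with 56% or 36% events at 12 months; deaths to disability in the ratio 24:32; disability dated at the next attended Rankin visit; 10% loss, with loss once disabled at 1 or 5 times the usual rate. The comparator is censoring at the last Rankin assessment.

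| Reading of last known alive | Unassessed person-months, control v intervention | Hazard ratio, stated rule v last Rankin |
|---|---|---|
| Last visit, no effect | 3.0 of about 1466 v 1.5 of about 1280 | 1.0007 v 1.0001 |
| Last visit, 56% v 36% | 2.9 v 1.7 | 0.5285 v 0.5282 |
| Traced to the end, no effect | 85 v 74 | 1.001 v 1.008 |
| Traced, no effect, 5× loss if disabled | 101 v 90 | 0.979 v 0.988 |
| Traced, 56% v 36% | 84 v 97 | 0.533 v 0.537 |

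On the last-visit reading, 3.0/1466 ≈ 0.2% of control time is unassessed, and rejection rates are identical under the two rules. In the traced scenarios, type I error stays at about 4–5%. A stress case with 20% loss, 5× loss if disabled and no effect gives 0.982 v 1.004, a shift of about 0.02.

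**Step 3: 12-month event estimates at 10% loss, same model.** Relative to censoring at the last Rankin assessment, the Kaplan–Meier event proportion is lower by:
- at most about 0.1 point if censored at the last visit;
- 0.2–0.4 point if censored at a loss date about 2 months after the last visit (that interval is an assumption);
- 0.8–1.5 points if vital status is traced to the end.

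**The case against.** The strongest reply is that the rule is meant for mortality. It follows the all-cause mortality sentence and uses mortality wording, and a censoring date for the composite could be left to the analysis plan. This has some force, because the text is ambiguous. But the same section reports mortality as a proportion, which needs no censoring date, and the composite is the only outcome defined as a time. The more coherent reading is that the rule governs the composite, which makes it a stated rule that does not fit rather than an omitted detail.

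A second reply is that multiple imputation covers the gap. The sentence is general and not tied to missing Rankin scores, and a participant with a censoring date has a complete survival record, so nothing obviously triggers imputation.

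A third is that clinical and neurological examination takes place at visits without a Rankin score, so disability is not wholly invisible there. That is fair, but the endpoint is measured by Rankin score.

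The last is that the numerical effect is negligible. For the hazard ratio and the test at the planned loss, this stands.

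**Conclusion.** The point holds as a low-importance mismatch between the stated censoring rule and the primary endpoint. At 10% loss it lowers 12-month event estimates by up to about 0.1–0.4 point, or about 1 point if vital status is traced to the end. The hazard ratio moves by about 0.001 or less, or up to about 0.01 if traced. These sizes rest on the simulation assumptions listed in the working.

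Three stronger readings are tempting, and the documents do not support them.

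- A reader might infer that lost survivors count as disability-free for good. In a binary analysis, 56% v 36% would become 0.9 × 56 = 50.4% v 0.9 × 36 = 32.4%, with power at 124 per arm falling from 89.0% to 82.5%. The planned Kaplan–Meier, log-rank and Cox analyses remove censored participants from the risk set, and changing the censoring date would not recover disability arising after loss.
- A reader might infer that disabled survivors are censored. The endpoint definition excludes this: a participant who has reached disability has had the event.
- A reader might infer that unassessed time is generally longer in control. That is supported for scheduled visits in months 7–12. With traced vital status and the planned effect, the intervention arm accrues more (97 v 84 person-months).

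**What to change.** Replace the single rule with two.

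1. **Composite:** a participant who dies or meets the disability definition has an event. A survivor who has not met it is censored at the date of the last modified Rankin assessment.
2. **All-cause mortality, if analysed as a time:** survivors are censored at the date last known alive.

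The analysis plan should also say whether missing Rankin scores enter the multiple imputation, and how a death learned of after missed Rankin visits is handled in the composite.

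The cost is a sentence or two in the protocol or analysis plan. It needs no new data, no extra visits and no change in sample size. Trial status records that recruitment had not begun at this version, so the change can be made before any outcome is seen.
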